### Eligibility criteria

The inclusion criteria will be as follows: (1) levels I or II on the Gross Motor Function Classification System (GMFCS) [23] and on the Expanded and Revised Gross Motor Function Classification System (GMFCS-ER) [24]; (2) aged 7 to 14 years (both sexes) with CP type spastic hemiplegia; and (3) having mild or no cognitive impairment. Exclusion criteria will include patients with other than CP neurological disorders, epilepsy, and uncorrected vision or hearing. Participants with access to a Nintendo Wii at home before the intervention commences will be also excluded.

### Interventions

This study will compare the effects of low-cost virtual reality delivered through FtF and TR modalities. The low-cost virtual reality will consist of using a Nintendo Wii balance board to play 4 exergames. In the FtF group, therapy will be provided by a physiotherapist with experience in the use of exergames for rehabilitation. In the TR modality, the intervention will be delivered by the patient’s parent or caregivers, who will be previously trained about how to deliver and assist exergames correctly and safely. In total, participants in both groups (FtF and TR) will receive 18 exergaming sessions divided in 3 sessions per week every other day (Monday, Wednesday, and Friday) over a period of 6 weeks. Each session will last for 25 minutes in which each participant will perform three series of exergames with 2-minutes rest in between games as we previously described [22]. The first two series will include Snowboard, Penguin Slide, and Super Hula Hoop. The first series will be played with arms on the side and the second one with hands on the waist to avoid the potential effect of training under one or the other strategy. The third series will be deep breathing in the Yoga game. During the first 2 weeks of training (first 6 sessions), patients will receive manual guidance and verbal instructions after which (7^th^ session onwards) only verbal instructions will be provided by the parents, caregiver, or physiotherapist.

In the Snowboard exergame patients will score by swaying (CoP displacement) in the anterior-posterior direction to swerve around flags whereas in the Penguin Slide patients will sway in the medial-lateral direction to score by catching fish while maintaining a pinguin within a continuously tilting platform. Finally, in the Hula Hoop game, patients will maintain hoops on the waist of an avatar by swaying in a (anti)clockwise circular pattern. The aim in the Yoga game will be to stand as quite as possible, first with eyes open and then with the eyes closed.

The designed low-cost virtual reality programme will be based on previous studies that have demonstrated similar interventions can effectively train postural control.^11^ For all participants in both groups (FtF and TR), adherence will be encouraged through telephone reminders. No modifications of the intervention protocols throughout the study are considered at this stage.

### Outcomes

Differences between the effects of FtF and TR using low-cost virtual reality on postural control will be assessed using posturographic measures. In brief, posturography assesses postural control through measures of the CoP sway, of which the most commonly used are sway area (CoP_area_), and trajectories and velocities in the medial-lateral (V_ML_) and anterior-posterior (V_AP_) directions [25]. These CoP variables have been shown to be sensitive in determining changes in postural control due to training in young adults [26], patients with post-stroke hemiparesis [27], patients with Parkinson’s disease [28],^,^ and children with CP [26–28].

Primary outcome in this study will be the CoP_area_, which has been shown to be a reliable and valid measure of postural control in different clinical and nonclinical populations [22–28]. The CoP_area_ is an overall measure of the ability of the balance control system to maintain a stable upright posture, to note, higher CoP_area_ values indicate poorer balance control. The CoP_area_ has been previously and extensively used as an outcome measure of interventions aimed at improving balance control in children with atypical motor control development [29–32].

The secondary outcome measures of this study will be the standard deviation (CoP_SD_), V_ML_ and V_AP_. The CoP_SD_ is a measure of the variability of CoP displacements whereas the CoP velocity is a measure of the ability to react to changes in posture with larger values indicating poorer balance control. The latter is due to late postural adjustments lead to large CoP excursion that demand rapid corrections to maintain stability [25]. If CoP_SD_ and/or V_ML_ and V_AP_ are reduced, this will be interpreted as a beneficial effect on the intervention.

Tertiary outcome measures of this study will be the Modified Modified Ashworth Scale (MMAS) for lower limbs (ankle and knee flexor-extensor musculature), Modified Ashworth Scale (MAS) for upper limbs (elbow and wrist flexor-extensor musculature), timed up-and-go (TUG) tests, the timed one-leg standing (TOLS) and 6-minute walk test (6MWT). These are widely used clinical measures of spasticity (MMAS and MAS) and overall physical performance, which include some aspects of postural control (TOLS) and dynamic balance (TUG and 6MWT). Reductions in the MAS and MMAS spasticity scores, as well as TUG and 6MWT reduction and TOLS increase will be interpreted as beneficial effects of the interventions at a physiological and motor performance levels, respectively (Fig 2).

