**Methods:**

This is a registered randomized controlled clinical trial protocol (ACTRN12621000117819). Eighteen sessions of low-cost virtual reality therapy will be provided through both, FtF and TR modalities using a Nintendo Wii balance board. Each programme will last for 6 weeks and will consist of 3 sessions per week of 25 minutes each. Twenty patients diagnosed with cerebral palsy—spastic hemiplegia will be recruited for each group: FtF or TR (n = 40). Participants will be assessed at baseline, by the end of weeks 2, 4, and 6, and at weeks 8 and 10 (post-intervention follow-ups). The primary outcome will be the Center of Pressure sway area (CoP_area_); secondary outcomes will be standard deviation and velocity of the CoP in the mediolateral and anterior-posterior directions; tertiary outcomes will include the Modified-Modified Ashworth Scale for lower limbs, Modified Ashworth Scale for upper limbs, timed up-and-go tests, the timed one-leg standing and 6-minute walk test.

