### Sample size

Using centre-of-pressure (CoP) sway area (CoP_area_) results from earlier studies [11, 22], to achieve an 80% statistical power with an alpha level of 0.05 and considering a standard deviation of 4.974 cm^2^ (after a 6-weeks intervention), we calculated a required minimum of 20 participants in each group (FtF and TR). This sample size includes a 5% attrition, which yields a total sample size of n = 40. Sample size calculation was performed using GRANMO (Institut Municipal d’investigació Médica, Barcelona, Spain). Once the investigative work has been carried out, the sample size will be verified again, and the estimation error will be adjusted. Feasibility of this study is ensured by our previous work with similar sample size, target population, outcomes, and funding [10].

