### Data analysis

Descriptive statistics will be used to summarize the demographic and clinical characteristics in both intervention groups, and unpaired t-tests and chi-square tests will be used for comparisons. For all outcome measures, the Shapiro–Wilk and Levene tests will be used to measure the normality and homogeneity of the variance, respectively. If the assumptions of normality are met, a t-test will be employed, otherwise we will use Mann–Whitney U test to determine differences between the FtF and TR groups. Also, if the assumptions of normality are fulfilled, we will employ a repeated measures analysis of variance (RM-ANOVA), otherwise will be use Friedman’s test. Post-hoc pairwise comparisons will be used to determine the interventions effect over time for each group (FtF and TR). Cohen´s *d* will be used to report effect sizes for the CoP variables. To allow repeated measures analysis, missing data will be adjusted by 1) replacing with the non-missing average values for each variable/week, and 2) performing multiple imputations. Both methods will be used to make sure that the results were concordant. For all analyses, a *p*-value ≤0.05 will be considered statistically significant. All statistical analyses will be performed using IBM-SPSS 20.0 (SPSS Inc., Armonk, NY, USA).

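### The protocol reads a fall in the 6-minute walk test as benefit, which reverses the direction of this tertiary outcome

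*Protocol article*

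**What the plan says.** The Outcomes section lists five tertiary measures: the Modified Modified Ashworth Scale (MMAS, lower limbs), the Modified Ashworth Scale (MAS, upper limbs), TUG, TOLS and 6MWT. It presents the last three as measures of physical performance, "which include some aspects of postural control (TOLS) and dynamic balance (TUG and 6MWT").

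It then sets the direction of benefit. Lower spasticity scores are beneficial, and for the performance tests "as well as TUG and 6MWT reduction and TOLS increase will be interpreted as beneficial effects of the interventions". The sentence therefore distinguishes measures where lower is better from the one where higher is better, and places the 6MWT in the first set, next to the TUG.

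No other section gives a direction, unit or metric for the 6MWT. The abstract only names the tests ("timed up-and-go tests, the timed one-leg standing and 6-minute walk test"), Intervention timeline gives only the visit weeks, and Data analysis names the tests and the p-value threshold.

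**The concern.** TUG and 6MWT differ in what is held fixed. In the TUG the task is fixed and the time is recorded, so a smaller value is better. In the 6MWT the time is fixed and the child covers as much ground as the test allows, so a smaller value is worse. One direction cannot serve both.

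At stake is the meaning of the walking result. The Discussion says the clinical measures will show effects beyond postural control and gives walking as an example, and the 6MWT is the only listed test named for walking. Under the stated rule, a group that lost distance would be described as having benefited, and a group that gained distance as having got worse. If the analysts instead use the opposite direction without amending the text, they depart from the only published rule for this outcome, and a reader cannot tell a correction from a choice made after seeing the data.

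**Working it through.** The article states no figure for the 6MWT, so there is nothing to reproduce. The check is one of text and logic.

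**1. Inputs.** The direction of benefit and the list of measures come from Outcomes. The assessment times come from Intervention timeline. The tests and threshold come from Data analysis. The planning values come from Sample size.

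**2. Direction of each tertiary measure.**

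| Measure | What varies | Better when | Protocol counts as benefit | Agree? |
|---|---|---|---|---|
| MMAS, MAS | spasticity score | lower | reduction | yes |
| TUG | time for a fixed task | lower | reduction | yes |
| TOLS | time held on one leg | higher | increase | yes |
| 6MWT | distance in a fixed time (inferred) | higher | reduction | **no** |

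**3. Why the 6MWT result must be distance.** Duration is fixed at 6 minutes by the test's name, so completion time cannot be the result. Distance = 6 min × mean speed, so change in distance = 6 min × change in mean speed. The two changes have the same sign: a reduction in the result is a reduction in walking speed.

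**4. How far the error reaches.** One of five tertiary measures is affected. The post-baseline assessments are at weeks 2, 4, 6, 8 and 10, which is five. Data analysis provides both a comparison over time within each group and a comparison of FtF with TR, and the rule governs the reading of both.

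**5. What does not change.** Calling the opposite direction beneficial amounts to multiplying the change by −1. For a t-test, t becomes −t and the two-sided p-value depends only on |t|. As an illustration with invented changes of 10, 20, 30, 15 and 25, the mean is 20, the SD is √62.5 = 7.91, the standard error is 7.91/√5 = 3.54, and t = 20/3.54 = 5.66 on 4 degrees of freedom, giving two-sided p = 0.0048. With all signs reversed, t = −5.66 and p is again 0.0048. The absolute size of Cohen's *d* is likewise unchanged. The p ≤ 0.05 rule in Data analysis names no one-sided alternative.

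**6. Link to the primary analysis.** The sample size uses the SD of the primary outcome, centre-of-pressure sway area ("considering a standard deviation of 4.974 cm^2^ (after a 6-weeks intervention"). The 6MWT enters neither that calculation nor the allocation.

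**The case against.** The best reply is that this is a drafting slip of little consequence. The outcome is tertiary and the last one listed, the data and estimates are the same whichever direction is called beneficial, and anyone who knows the test would notice. Most of that stands and sets the rating. It does not remove the error: the sentence is complete, admits no reading in which an increase is a benefit, and is not corrected elsewhere.

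A second reply is that the article never says the 6MWT result is distance. That is true, and distance should be labelled an inference. The fixed duration makes it a strong one, and the missing unit is a reason to state the metric in the same edit.

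A reader might also infer more than the text supports:

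- *That children would be counted as improved.* The article has no responder definition. It says only how a change will be interpreted, and a false report follows only if the rule is applied literally.
- *That the error upsets a non-inferiority conclusion.* The introduction hypothesises that TR will be as effective as FtF, but Data analysis contains no non-inferiority test or margin for the direction to enter.
- *That the abstract repeats the error.* It lists the test without a direction and needs no change on this point.

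**Conclusion.** The stated direction of benefit for the 6MWT is reversed. Applied as written, it turns the interpretation of one of five tertiary outcomes upside down, within groups over time and for TR versus FtF, at all five post-baseline assessments. It has no effect on the primary outcome, the sample size, the estimates or two-sided p-values.

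The conclusion rests on two assumptions: that the 6MWT result is distance walked, which follows from its fixed duration, and, for the statement about p-values only, that the tests are two-sided. This is a should-fix correction to an outcome definition. The documents do not support a claim that the trial's main conclusion is at risk.

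**What to change.** State in Outcomes that the 6MWT result is the distance walked, in metres, and replace the interpretation sentence with:

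*Reductions in MAS, MMAS and TUG time, and increases in TOLS time and 6MWT distance, will be interpreted as beneficial.*

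Use the same directions when interpreting the within-group changes and the TR versus FtF comparison. Record the change as a dated correction, ideally before outcome data by group are examined, so that it cannot be taken for a choice made after the results. The cost is one sentence, with no change to assessments, data collection, sample size or statistical tests.

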**Fig 2 pone.0268163.g002:**
[figure not shown]
SPIRIT schedule of enrolment, interventions and assesments.

### Intervention timeline

Participants will be assessed at baseline, by the end of weeks 2, 4, and 6, and at weeks 8 and 10 (post-intervention follow-ups) using posturography and clinical measures.

### Recruitment

Children and adolescents with congenital SHE-CP will be recruited from the Rehabilitation Institute, Talca, Chile. This is an outpatient clinic that provides rehabilitation services to patients with neurological disorders including CP children. It is noteworthy, that patients from this centre will have little or no experience using a Nintendo Wii balance board. An experienced staff of health professionals, comprised of a physician and two physical therapists, will recruit participants according to the inclusion/exclusion criteria. Screening for potential participants will continue until the calculated sample size is achieved.

### Allocation

Participants will be randomly assigned to either control (FtF) or experimental group (TR) with a 1:1 allocation as per a computer-generated randomization schedule stratified by site and the baseline score of the Action Arm Research Test (ARAT; < = 21 versus >21) using permuted blocks of random sizes. The block sizes will not be disclosed, to ensure concealment. This statistical methodology is adjusted to the randomized and block design, allowing feasibility and affordability to carry out this clinical trial.

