### Study setting

This study will compare the effect of low-cost virtual reality in two distinct settings. The first setting will be clinical (Telerehabilitation Technology Centre and Neurosciences in Human Movement, Universidad de Talca, Chile) and in which low-cost virtual reality will be delivered in a FtF modality (control group) with therapist interacting directly with the patient. The second setting will be a remote facility with no therapist on-site for the delivery of low-cost virtual reality through TR. The default TR setting will be at-home, however, if a participant does not have adequate access to space and/or equipment, TR will be delivered at school, or rehabilitation centre. To note, in the latter cases (school and rehabilitation centre) no therapist will be involved in the TR delivery. All assessments will be conducted at the same facility in which the therapy will be delivered.

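### Randomisation is stratified by an arm-function score with no stated link to standing sway and by a site factor that cannot work as a stratum, so no balance is forced on balance severity

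*Protocol article*

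**What the plan says.** The Allocation section assigns children to face-to-face (FtF) or telerehabilitation (TR) delivery "with a 1:1 allocation as per a computer-generated randomization schedule", which is "stratified by site and the baseline score of the Action Arm Research Test (ARAT; < = 21 versus >21". Within strata the schedule is built "using permuted blocks of random sizes", and how large these are is kept secret.

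Four other sections bear on whether these factors can do their job:

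- **Recruitment:** children "will be recruited from the Rehabilitation Institute, Talca, Chile". No second recruiting centre is named.
- **Study setting:** FtF is given in one place: "The first setting will be clinical (Telerehabilitation Technology Centre and Neurosciences in Human Movement, Universidad de Talca, Chile"). TR takes place in the child's home unless room or equipment is lacking there; a school or a rehabilitation centre is then used instead. On measurement the section adds: "All assessments will be conducted at the same facility in which the therapy will be delivered".
- **Eligibility criteria:** children must be at "levels I or II on the Gross Motor Function Classification System (GMFCS"), so the level is known before allocation.
- **Outcomes:** the primary outcome is CoP sway area, the secondary outcomes are other CoP measures, and the tertiary outcomes are two spasticity scales, timed up-and-go, one-leg standing and the 6-minute walk. ARAT is not among them.

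**The concern.** A stratification factor earns its place by being scored before allocation and by predicting the outcome. In this article neither is shown for ARAT, and site has no workable definition. GMFCS level, a graded measure of gross motor function that must be known at screening, is not used.

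With 20 children per arm, simple chance can leave one arm with noticeably more of the more affected children. The stated hypothesis is that TR is as effective as FtF, and under it a chance difference in severity can hide a real difference between the arms or imitate one. The Data analysis section names no baseline covariate for the between-group comparison. A fuller analysis plan may do so, but the text at hand does not offset an imbalance.

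**Working it through.** The plan gives no figure for the effect of its stratification, so there is none to reproduce. The inputs from the Sample size section are 20 per arm, 40 in total, and an SD of 4.974 cm². All other values below are marked as assumptions.

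**1. Is ARAT listed as a measurement?** The Abstract, Eligibility criteria, Outcomes, Intervention timeline and Data collection sections do not name it. The only upper-limb measure is the Modified Ashworth Scale. The timeline mentions posturography and clinical measures in general terms. Fig 2 could list ARAT but is not shown.

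**2. Can site be a stratum?** There are two readings.
- *Recruitment site:* one institute, so one level and no effect. The scheme reduces to two ARAT strata.
- *Place of delivery or assessment:* the university centre for FtF; home, school or rehabilitation centre for TR. These places follow from the assigned arm, so they cannot define groups within which both arms are allocated.

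**3. Chance imbalance in an unstratified factor.** Assume that 20 of the 40 children are at GMFCS level II and that ARAT stratum is unrelated to level. The number X in one arm of 20 is then hypergeometric:

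P(X = x) = C(20, x) × C(20, 20 − x) / C(40, 20)

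- P(X = 10) = 184,756² / 137,846,528,820 = 0.2476
- P(X = 9) = P(X = 11) = 167,960² / 137,846,528,820 = 0.2047
- P(X = 8) = P(X = 12) = 125,970² / 137,846,528,820 = 0.1151

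P(12 versus 8 or worse) = 1 − 0.2476 − 2 × 0.2047 = 0.343.

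P(13 versus 7 or worse) = 0.343 − 2 × 0.1151 = 0.113.

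Range over the assumed number at level II:

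| Children at level II (assumed) | P(arms differ by 4 or more) | P(arms differ by 6 or more) |
|---|---|---|
| 8 | 0.235 | 0.044 |
| 12 | 0.301 | 0.082 |
| 20 | 0.343 | 0.113 |

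**4. What that means in cm².** Assume that level II differs from level I by 0.5 to 1.0 SD of sway area; the article gives no figure. A 12-versus-8 split is a difference in proportions of 12/20 − 8/20 = 0.2.

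- Shift in TR − FtF: 0.2 × 0.5 × 4.974 = 0.50 cm², up to 0.2 × 1.0 × 4.974 = 0.99 cm².
- Standard error of the difference: 4.974 × √(2/20) = 1.57 cm².
- Ratio: 0.50/1.57 = 0.32 to 0.99/1.57 = 0.63 standard errors.

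**5. What balancing ARAT could contribute.** For a continuous baseline such as sway area, the difference in arm means has SD √(2/20) = 0.316 in SD units. P(imbalance ≥ 0.5 SD) = 2 × [1 − Φ(0.5/0.316)] = 0.114. Balancing a stratum that correlates r with sway area multiplies the variance of the imbalance by 1 − r². The article states no r, so the values are assumed:

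| r (assumed) | Variance removed | P(imbalance ≥ 0.5 SD) |
|---|---|---|
| 0 | 0% | 0.114 |
| 0.1 | 1% | 0.112 |
| 0.3 | 9% | 0.097 |
| 0.5 | 25% | 0.068 |

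ARAT helps materially only if its correlation with sway is substantial. The same formula governs any replacement factor.

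**The case against.** The strongest reply is that a reader could take the criticism well beyond the text. Four such readings are tempting.

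- **The allocation cannot be run because no ARAT score exists.** The Allocation section refers to a baseline ARAT score, which implies that one is taken. The timeline speaks of clinical measures generally, Fig 2 is not shown, and an article need not list every screening test. The step fails as written only if ARAT is not in fact measured.
- **The stratification protects against nothing.** No ARAT–sway correlation is given, zero or otherwise, and ARAT may partly track the severity of the hemiplegia. That it was carried over from another trial would be a guess.
- **The strata leave incomplete blocks.** With site reduced to one level there are two ARAT strata. Stratifying on GMFCS level also gives two, so this does not separate the plan from the remedy.
- **The comparison is biased.** It is not. Allocation stays random, blocking still balances arm sizes, and ordinary standard errors already allow for chance imbalance.

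On site, it could be added that lack of space or equipment at home is a characteristic of the child's circumstances that might be known before allocation. That is so, but the article does not say that site means this. It could also be noted that no GMFCS–sway relation is stated and that eligibility is already confined to two levels. That stands too, so the cm² figures are only illustrative.

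The reply leaves the main point in place: the article neither justifies ARAT for a sway outcome nor gives site a meaning under which it works.

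**Conclusion.** The concern holds in limited form. The chosen stratifiers are an arm-function score with no stated relevance to standing sway area, absent from every visible list of measures, and a site factor that is either a single level or fixed by the arm. As a result, the scheme forces no balance on baseline balance severity.

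The chance of a 12-versus-8 or worse split on GMFCS level is 34% if half the children are at level II, and 24% to 30% for an arm difference of the same size if 8 or 12 are. Such a 12-versus-8 split would move the estimate by about a third to two thirds of its standard error, if the levels differ by 0.5 to 1.0 SD. The prevalence and the difference between levels are both assumptions.

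The cost is lost balance and precision in a small trial. The documents do not support a claim of bias, of an invalid randomisation, or of an allocation that certainly cannot be carried out. This should be fixed, and it can largely be recovered in the analysis.

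**What to change.** **Before enrolment:** drop site; replace ARAT with GMFCS level (I versus II), already determined at screening; and use permuted blocks within level. Within each level the arms can then differ by at most half of the last block. Adjust the TR–FtF comparison for GMFCS level and for baseline CoP area, which is measured at the baseline visit. The cost is a regenerated randomisation list and a sentence in the analysis section; the sample size does not change.

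**If the sponsor wishes to keep ARAT:** state when and by whom it is scored before allocation, add it to the baseline assessments, and justify both its relation to sway area and the cut at 21.

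**If enrolment has begun:** report the stratification actually used, including what site meant in practice and whether ARAT was scored, and make the same baseline adjustment in the analysis. This needs no new data.

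In either case the Allocation section should be reconciled with Study setting, Eligibility criteria, Outcomes, Intervention timeline and Recruitment.

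### Allocation is stratified by site and ARAT, but the named between-arm tests ignore the strata; if the strata predict CoP area, the test is conservative and some power is forgone

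*Protocol article*

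**What the plan says.** The Allocation section of the protocol article describes a "computer-generated randomization schedule stratified by site and the baseline score of the Action Arm Research Test" (cut at 21), "using permuted blocks of random sizes", with 1:1 allocation. It ends: "This statistical methodology is adjusted to the randomized and block design, allowing feasibility and affordability to carry out this clinical trial".

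The Data analysis section fixes the between-arm comparison: "a t-test will be employed, otherwise we will use Mann–Whitney U test to determine differences between the FtF and TR groups". RM-ANOVA or Friedman's test follows for change over time. Site, ARAT category and other covariates appear in none of the named tests.

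The Sample size section gives 20 children per arm, 5% attrition included, for 80% power at alpha 0.05 with an SD of 4.974 cm². It does not state the difference to be detected.

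**The concern.** Blocking within strata forces the arms to be nearly balanced on the strata, which removes between-stratum variation from the arm difference. An unpaired t-test does not know this. Its pooled variance still contains the between-stratum part, so its standard error exceeds the real sampling variability of the difference. The Mann–Whitney test ignores the strata in the same way.

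What is at stake is efficiency. If the strata carry information about CoP area, the design has bought precision that the analysis does not use. With about 20 children per arm there is little to spare.

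**Working it through.** **Inputs from the protocol article.** SD 4.974 cm², 20 per arm, 5% attrition, 80% power, alpha 0.05 (Sample size); stratified permuted blocks, 1:1 (Allocation); unpaired t-test (Data analysis).

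**Assumptions.** Two-sided testing, since sidedness is not stated. R², the share of CoP-area variance explained by the strata, is not given and is ranged from 0 to 0.5.

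**The plan's own figure.** The 20 per arm cannot be reproduced without a detectable difference. The attrition step is consistent: 19/0.95 = 20. Solving backwards with 19 evaluable per arm gives

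δ = 4.974 × √(2/19) × (1.960 + 0.842) = 4.52 cm², or d = 0.91.

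The exact t-based calculation with 20 per arm also gives 4.52 cm². This value serves only as a reference effect.

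**Size of the mismatch.** With strata balanced by design:

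- standard error reported by the t-test ≈ SD × √(2/n)
- true sampling SD of the difference ≈ SD × √(2/n) × √(1−R²)
- ratio = 1/√(1−R²)

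With n = 19 the first is 4.974 × √(2/19) = 1.61 cm². At R² = 0.3 the second is 1.61 × √0.7 = 1.35 cm², so the reported value is about 20% too wide. Simulation gave the same pair, 1.61 and 1.35.

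**Consequences, normal approximation.** Write k = √(1−R²).

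- Type I error, unadjusted: 2 × [1 − Φ(1.960/k)]
- Power, unadjusted: Φ(0.842/k)
- Power, adjusted: Φ(2.802/k − 1.960)

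| R² | SE ratio | Type I, unadjusted | Power, unadjusted | Power, adjusted |
|---|---|---|---|---|
| 0 | 1.00 | 5.0% | 80.0% | 80.0% |
| 0.05 | 1.03 | 4.4% | 80.6% | 82.0% |
| 0.10 | 1.05 | 3.9% | 81.2% | 84.0% |
| 0.25 | 1.15 | 2.4% | 83.4% | 89.9% |

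**Simulation, 40 children.** One two-level stratum split 50:50, blocks of 2 or 4, d = 0.909, 20,000 trials per setting. Power, t-test versus linear model with arm and stratum:

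- R² = 0: 80.0% versus 79.9%
- R² = 0.05: 80.6% versus 82.0%
- R² = 0.10: 81.0% versus 83.8%
- R² = 0.25: 82.6% versus 89.5%, with type I error 2.4% versus 4.8%

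**Second simulation, separate code, 38 evaluable children.** 6,000 trials per setting, power in the same order:

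- R² = 0: 78.1% versus 78.0%
- R² = 0.1: 79.2% versus 81.9%
- R² = 0.3: 80.8% versus 89.9%, with type I error 1.8% versus 4.9%

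Four strata gave nearly the same results. Values just under 80% at low R² arise because 4.52 cm² was solved with the normal formula for 19 per arm; the t-based value is 4.65 cm². They occur with and without adjustment, so the strata are not the cause.

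**The case against.** **The Allocation sentence.** A reader might infer that the protocol contradicts itself, promising an adjusted analysis and then not providing one. The text does not carry that. "This statistical methodology is adjusted to the randomized and block design" closes the section on randomisation, follows directly on the block scheme, names feasibility and affordability as its benefit, and does not point to Data analysis. It can be read as describing only the allocation method. This objection stands, and the point does not depend on the sentence.

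**R² may be small.** ARAT scores the arm, while the outcome is sway in standing. All children have spastic hemiplegia at GMFCS level I or II, and Recruitment names one institute. This stands. The loss passes 5 points only at R² of roughly 0.2 or more, and nothing in the document supports or excludes such a value.

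**No planned property is breached.** A reader might infer an invalid test or a trial short of its planned power. Neither follows: the t-test errs on the conservative side, and its power rises slightly with R². The loss is relative to a better analysis.

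**Effect on the claim that TR is as effective as FtF.** One might argue that an inflated standard error favours this conclusion if a non-significant p-value is read as support, or that it widens the confidence intervals. The Data analysis section states neither that reading nor a confidence interval; it plans p-values and Cohen's d. Using difference tests for such a hypothesis is a separate matter that stratum terms would not cure.

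**Repeated measures.** If arm enters the RM-ANOVA, its arm-by-time contrast already removes a constant stratum effect. This is correct, and it limits the point to the t-test and Mann–Whitney comparisons.

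**Left to the analysis plan.** Covariate choice often is. Here, though, the article names specific tests that have no place for a stratum term, so the point concerns what is stated rather than what is absent.

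**Conclusion.** The point holds as one of efficiency. The named between-arm tests do not reflect the stratified allocation. If the strata predict CoP area, the standard error is too wide and power is forgone relative to a stratum-adjusted analysis: about 1 to 3 points at R² of 0.05 to 0.10, about 7 points at 0.25, nothing at 0. These figures assume two-sided testing, a reference effect of about 0.91 SD, evenly sized strata and near-complete data. The true R² is unknown and may lie at the low end. The adjustment is worth making because it costs almost nothing, not because the planned test is invalid.

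**What to change.** In Data analysis, replace the unpaired t-test for CoP area with a linear model containing arm and the randomisation strata actually used as fixed effects: ARAT category, and site if there is more than one. Site here must mean a factor known before randomisation. The place of delivery differs by arm under Study setting and cannot serve. As the rank-based fallback, replace the Mann–Whitney test with the van Elteren stratified Wilcoxon test.

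The cost is wording and 1 or 2 of 38 degrees of freedom. The stratum values are already needed to randomise. If the strata turn out uninformative, power is essentially unchanged (79.9% versus 80.0% in the simulation).

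As a secondary point, reword the closing Allocation sentence to say whether it refers to the randomisation or the analysis. Deleting it without changing the tests would alter no result.
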